### Randomization and blinding

A total of 260 participants will be randomly assigned to the *Guhong* group and the control group in a ratio of 1:1 by the method of using 260 opaque envelopes. Each envelope will be stuffed with a piece of paper. There are 260 pieces of papers in total, half of which have the words: “20 ml *Guhong* injection plus 250 ml 0.9% sodium chloride, ivd, qd” written on them and the other half have the words “270 ml 0.9% sodium chloride, ivd, qd” written on them. After all the opaque envelopes have been stuffed and sealed, they will be mixed evenly and distributed to each trial center.

When a sub-center accepts an eligible participant, the investigators will write the baseline information (including the subject’s hospital ID number, name, age and gender) on the cover of the envelope. Both investigators and participants will be blinded. Only drug administrators and dispensing nurses are responsible for opening the envelope to know the group allocation and perform the interventions according to the written instructions on the paper, but they won’t be involved in recruitment, recommendations, data collection and data analysis. Both the *Guhong* injection and placebo are administered using a photophobic infusion set to avoid the subjects being aware of the group information. All investigators, outcome assessors and data analysts will be blinded to collect and summarize the data which is only based on a subject’s baseline information until the completion of the visit and analysis.

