### Participants and recruitment

We will recruit patients who meet the criteria for inclusion by advertising on hospital notice boards, posting recruitment information in network communication groups or by being recommended by outpatient and inpatient physicians. A total of 260 eligible participants will be recruited in the following six hospitals: (1) Guangdong Provincial Hospital of Traditional Chinese Medicine, (2) Guizhou Provincial Hospital of Traditional Chinese Medicine, (3) Second Affiliated Hospital of Guizhou University of Traditional Chinese Medicine, (4) Foshan Traditional Chinese Medicine Hospital, (5) Shenzhen Longgang District Hospital of Traditional Chinese Medicine and (6) Yangjiang People’s Hospital. These six trial centers are all first-class hospitals in China, with advanced cardiovascular interventional departments, excellent medical teams and many inpatient beds. Especially the Guangdong Provincial Hospital of Traditional Chinese Medicine, which has the largest number of outpatients among the TCM hospitals in China and rich experience and achievements in the research of integrated Chinese and western medicine. So, the first center will recruit 80 patients, with 36 for each of the remaining centers.

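### One shuffled pool of 260 envelopes is split over six centres, so the 1:1 ratio is controlled only for the whole trial and not within centres

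*Protocol article*

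**What the plan says.** The section *Randomization and blinding* sets the method out step by step. Patients are assigned "in a ratio of 1:1 by the method of using 260 opaque envelopes". The slips are split evenly between the two regimens: "There are 260 pieces of papers in total, half of which have the words" for one arm, and the rest carry the other. Then: "After all the opaque envelopes have been stuffed and sealed, they will be mixed evenly and distributed to each trial center".

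On enrolment, "the investigators will write the baseline information (including the subject’s hospital ID number, name, age and gender) on the cover of the envelope". Opening is kept apart from recruitment: "Only drug administrators and dispensing nurses are responsible for opening the envelope to know the group allocation", and those staff take no part in recruitment, data collection or analysis. Investigators, assessors and analysts are "blinded to collect and summarize the data which is only based on a subject’s baseline information".

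The section *Participants and recruitment* sets the quotas: "the first center will recruit 80 patients, with 36 for each of the remaining centers".

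**The concern.** Mixing the sealed envelopes is the sequence generation. Because the whole pool is mixed before it is divided, each centre receives a random draw from it. This is a stated procedure and not a detail left to a fuller document, and it does not control the split within a centre.

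That matters because the primary outcome (*Primary outcome*, Table 3) grades change in angina and ECG in terms such as significant improvement or a substantially normal ECG, which centres may apply differently. If one arm is over-represented in a lenient centre, the crude comparison takes in part of the centre difference. Overall balance is also conditional: the section *Interim analyses and stopping guidelines* allows a stop near the halfway point, when many envelopes would be unused.

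A second, weaker point is that the envelopes are mixed after sealing and the only identifier described is the patient's details, added at enrolment. Nothing described would show that envelopes were used in a set order.

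**Working it through.** **Inputs.** 260 envelopes, 130 per arm (*Randomization and blinding*); centre sizes 80 and 5 × 36 (*Participants and recruitment*); rates 81.82% and 93.94%, two-sided α = 0.05, β = 0.2 (*Sample size*).

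**The plan's own figures.** 80 + 5 × 36 = 260, which agrees with the envelope count. The unpooled two-proportion formula gives 109.9 per group, so 110 against the stated 111, which is close enough. The allocation method does not change the sample size.

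**Split within one centre.** The number X of Guhong envelopes in a centre of size m is hypergeometric, with variance m × ½ × ½ × (260 − m)/259. The arm difference is 2X − m.

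- m = 36: variance 9 × 224/259 = 7.78, SD 2.79, SD of the difference 5.58. P(22:14 or worse, either way) = 20.8%; 23:13 or worse 10.5%; 24:12 or worse 4.7%; exactly 18:18 14%.
- m = 80: variance 20 × 180/259 = 13.90, SD 3.73, SD of the difference 7.46. P(45:35 or worse) = 22.6%.

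**All centres together** (200,000 simulated divisions of the pool). At least one of the five 36-patient centres is at 22:14 or worse with probability 67%, 23:13 or worse 41%, 24:12 or worse 21%. All six exactly balanced: below 0.01%. Complete blocks of 4 within centre (36 = 9 × 4, 80 = 20 × 4) would make every filled centre exactly balanced.

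**Cost in precision if the analysis is stratified by centre.** The information in a centre relative to an even split is 4X(m − X)/m². For 22:14 it is 1,232/1,296 = 0.95; for 24:12 it is 1,152/1,296 = 0.89. The expected loss is 4 Var(X)/m²: 4 × 7.78/1,296 = 2.4% for m = 36 and 4 × 13.90/6,400 = 0.87% for m = 80. Over the trial: (180 × 0.0240 + 80 × 0.0087)/260 = 1.9%, or about 5 patients.

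**Cost if it is not stratified.** The documents give no rates by centre, so assume a patient-weighted between-centre SD of 5 to 10 percentage points. The average planned rate is (81.82 + 93.94)/2 = 87.88%, with variance 0.8788 × 0.1212 = 0.1065. The between-centre share is 0.05²/0.1065 = 2% to 0.10²/0.1065 = 9%. The SD of the shift that centre imbalance causes in the rate difference is 0.05 × √(2/130) = 0.6 to 0.10 × √(2/130) = 1.2 percentage points. For comparison, the planned difference is 12.12 points and its standard error is √[(0.8182 × 0.1818 + 0.9394 × 0.0606)/130] = 4.0 points.

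**Stop at half.** If 130 of the 260 envelopes are used, treated as a random half of the pool, the variance of X is 32.5 × 130/259 = 16.3 and the SD of the difference is 8.1. P(70:60 or worse) = 26%. At the edge of the 95% range, 57:73, the information is 4 × 57 × 73/130² = 0.985, a loss of 1.5%.

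**The case against.** A well-mixed pool gives chance allocation, so centre imbalance has expectation zero and causes no bias. The variance p(1 − p) used for the sample size already contains between-centre variation, so nothing is added to the planned variance; only a possible gain is forgone. The early-stopping loss is negligible. All of this stands, and it limits the point to precision and to chance confounding in the one trial that will be run.

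A reader might infer that the envelopes are unnumbered, that no central list exists, and that concealment is therefore unverifiable or that envelopes could be freely swapped. The documents do not support that. The article never says the envelopes are unnumbered. It is a condensed account of a full protocol that is not shown, and such a document commonly holds numbering and custody details. The article does state real safeguards: opaque sealed envelopes, patient details on the cover, and opening by staff outside recruitment. These protect concealment and tie each used envelope to a patient. What remains is narrower: the steps described do not show that a sequence was followed or that no envelope was passed over.

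Adjustment for centre is commonly left to the statistical analysis plan, so the lack of a centre term in *Data management and statistical analysis* is not itself a fault. The term is proposed here as the remedy.

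**Conclusion.** The point holds as a weakness in a stated design choice. It is not an error that invalidates the allocation. By design the arms are 1:1 only over all 260 envelopes; a 36-patient centre has a 21% chance of 22:14 or worse, and about two trials in three would have at least one such centre. These counts assume perfect mixing, full use of the envelopes and centres that fill their quotas.

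In precision the size is modest: about 2% of information on average under a centre-stratified analysis, or 2% to 9% of variance left unexplained without one, if centre rates vary with an SD of 5 to 10 points. That last range is an assumption. The change is worth making because it is cheap and the outcome is partly subjective. The remark on sequence adherence carries lower confidence, since it rests on what a condensed article does not describe.

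**What to change.** 1. For patients still to be randomised, replace the unused envelopes with centre-specific, computer-generated permuted-block lists. Number the envelopes consecutively, use them in order, log each opening, and record the date of the change. Someone independent of recruitment, assessment and analysis should hold the list. It should not lie with the analysts at the Drug Clinical Research Center: that body is responsible for the statistical analysis, and the article requires analysts to stay blinded.
2. For all patients, stratify the primary comparison by centre (Cochran-Mantel-Haenszel) and include centre as a factor in the other models. State this before unblinding.

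**Cost.** The article reports enrolment under way at six centres, so part 1 means recalling envelopes mid-trial, reporting a two-phase allocation, and accepting an overall split that may differ slightly from 130:130. It also cannot undo imbalance already present. Part 2 costs nothing and should be done even if replacing the envelopes is impractical or recruitment has ended. The sample size does not change.

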### Emergency unblinding

If an emergency occurs, the patient group assignment should be unblinded and known to the drug administrators or dispensing nurses, and corresponding emergency measures will be taken. Researchers will report this special situation to the center’s principal within 24 h. At the same time, the cause of unblinding, the time of the emergency, the solution and the result must be filled in the case report form (CRF). Once the participant ‘s allocated intervention during the trials has been revealed, the case will be withdrawn and the data will be recorded on day 10 of the trial evaluation.

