## Methods/design

### Study design

This study is a multicenter, parallel, prospective, double-blind, randomized, placebo-controlled clinical trial. A total of 260 patients will be enrolled and randomly divided into the treatment and placebo groups. All patients will receive 10 consecutive days of treatment and follow-up for 8 weeks. Efficacy and safety data will be collected throughout the study. The study flow chart is shown in Fig. 1.

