### Interventions

On the basis of conventional western medicine treatment, the *Guhong* group will be given a 20-ml intravenous infusion of *Guhong* injection that was diluted with 250 ml 0.9% sodium chloride injection once a day, while the control group will be given 270 ml 0.9% sodium chloride injection as placebo treatment once a day. (*Guhong* injection is provided by China tonghua guhong pharmaceutical co. Ltd. The production batch number is 20190306 and each bottle has a capacity of 5 ml. The drug distributed to each center will be labeled with the statement “for trial only” and the information of the name, dosage, dosing plan, indications, storage conditions, expiratory date, manufacturer and so on. Each center has an independent manager responsible for receiving, handling, storing and distributing the medications.) The course of treatment is 10 days. On the day of enrollment and at the end of treatment, the clinical symptoms and signs of angina pectoris will be recorded, the quantitative table of TCM syndrome will be scored, the electrocardiogram (ECG) will be examined, and the indicators of inflammation, endothelial function, myocardial metabolites and related biochemical tests will be conducted. Moreover, patients will be followed up for 8 weeks after the end of treatment, including any improvement in angina pectoris and the TCM syndrome quantitative score. During the entire study period, participants will be visited for a total of four times by the investigators. Specific research process details are provided in Table 2.

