### Efficacy assessment

#### Primary outcome

The criteria for therapeutic efficiency evaluation is based on the principles for clinical research reports on cardiovascular drugs formulated by the National Health and Pharmaceutical Bureau of China [13] by comparing the anginal attack frequency and ECG changes before and after treatment in the two groups of participants. Specific evaluation criteria are shown in Table 3.

**Table 3 Tab3:** Evaluation criteria on the therapeutic efficiency

Three-graded criteria	Detailed description	Classification
Significant improvement	Anginal attacks disappeared or significantly improved, decreased by 80%; electrocardiogram (ECG) returned to normal or substantially normal	Significantly effective
Improvement	Anginal attacks improved or the frequency of anginal attacks decreased by 50–80%; the descending ST segment of the ECG rose ≥ 0.05 mV, and the ascending ST segment fell ≥ 0.05 mV, but still did not return to normal; or the T wave of the main ECG lead changed from flat to upright; or the T wave changed from inverted to shallow by more than 50%	Effective
No improvement	No change or even aggravation of anginal attacks, no decrease or even increase of the frequency of angina pectoris attacks, no change or even aggravation of ECG ST-T segment	No effect

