#### The average frequency of angina pectoris

The average frequency of angina pectoris from the first day of enrollment to the end of treatment and at 8 weeks of follow-up will be recorded in the CRF. Each participant will be instructed to record any change in their symptoms of angina pectoris in their patient diary daily.

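### Emergency unblinding withdraws the patient with only a day-10 record, against the planned 8-week follow-up and with no usable instruction for an emergency after day 10

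*Protocol article*

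**What the plan says.** The Emergency unblinding section of the protocol article sets a rule for any patient whose allocation is revealed: "the case will be withdrawn and the data will be recorded on day 10 of the trial evaluation". It makes no distinction by the timing or cause of the emergency. The same section also requires a record of the event: "the cause of unblinding, the time of the emergency, the solution and the result must be filled in the case report form (CRF").

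Other sections plan a longer course of observation:

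- Study design: "Efficacy and safety data will be collected throughout the study".
- Interventions: "The course of treatment is 10 days", and then "patients will be followed up for 8 weeks after the end of treatment, including any improvement in angina pectoris and the TCM syndrome quantitative score".
- The average frequency of angina pectoris: this outcome "from the first day of enrollment to the end of treatment and at 8 weeks of follow-up will be recorded in the CRF").

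The primary outcome is assessed "by comparing the anginal attack frequency and ECG changes before and after treatment in the two groups of participants", so its time point is the end of treatment. Data management and statistical analysis limits the FAS, the primary analysis set, to patients given 10 days of study infusion who have recorded observations. The safety set takes everyone who received any treatment.

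**The concern.** Revealing the arm changes who knows the allocation. It does not remove the reason to observe the patient. The protocol nevertheless makes it a ground for withdrawal, names one data point, and is silent about the weeks that follow.

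Patients leave through this route because something went wrong clinically. Their missing week-8 angina frequency, TCM score and later safety observations are therefore related to outcome, and the loss may differ between arms. If dosing also stopped early, the FAS condition can take the same patients out of the primary analysis.

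**Working it through.** **1. The rule set against the schedule.** Treatment lasts 10 days and follow-up 8 × 7 = 56 days, so the planned course ends at about day 10 + 56 = 66.

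| | Emergency up to day 10 | Emergency on about days 11 to 66 |
|---|---|---|
| Record named by the unblinding rule | Day-10 evaluation | Day-10 evaluation, which is already past |
| Cause, time, handling and result in CRF | Yes | Yes |
| Week-8 angina frequency and TCM score | Not provided for | Not provided for |
| Later safety follow-up | Not provided for | Not provided for |
| Safety set | Included | Included |
| FAS dosing condition | Failed if dosing ended before 10 days, even with a day-10 record | Can be met |

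The rule can be followed as written only in the first column. In the second, it points to a visit that took place before the emergency.

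**2. Does the broken blind require withdrawal?** Emergency unblinding makes the arm known to the drug administrators or dispensing nurses. Under Randomization and blinding, these staff open the envelopes, so they know the arm from the start, and they take no part in data collection or analysis. As written, the blind of investigators and assessors need not be broken. The list under Withdrawal criteria does not name unblinding as a reason.

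**3. Effect on power.** The documents give no unblinding rate, so the numbers lost below are assumptions. First, the plan's own sample size, using its formula with the usual squares:

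- Inputs from Sample size: πt = 0.9394, πc = 0.8182, two-sided α = 0.05, β = 0.2, 1:1 allocation.
- v = 0.9394 × 0.0606 + 0.8182 × 0.1818 = 0.2057.
- n = v × (1.960 + 0.842)² / (0.1212)² = 109.9, so 110 per group. The plan states 111, which is close enough.
- Attrition: 111 / 0.85 = 130.6. The plan uses 130.

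Power with m patients per arm is Φ(0.1212 / √(v/m) − 1.960):

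| Lost per arm | m | Power |
|---|---|---|
| 0 | 130 | 86% |
| 2 | 128 | 86% |
| 5 | 125 | 85% |
| 10 | 120 | 83% |
| 19 | 111 | 80% |

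**4. Effect on the estimate (illustration only).** Suppose the planning rates hold among patients who stay in the FAS, every patient dropped for short dosing would have counted as no effect, and the numbers dropped are as shown. The FAS difference is then 12.1 percentage points in every row. The difference among all 130 randomised per arm is πt(130 − wt)/130 − πc(130 − wc)/130, where wt and wc are the numbers dropped:

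| Dropped, Guhong / control | Guhong | Control | Difference, all randomised |
|---|---|---|---|
| 2 / 2 | 92.5% | 80.6% | 11.9 |
| 5 / 5 | 90.3% | 78.7% | 11.7 |
| 5 / 2 | 90.3% | 80.6% | 9.8 |
| 2 / 5 | 92.5% | 78.7% | 13.8 |

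A few patients hardly move power. If they fall unevenly between the arms, they can move the estimate by about 2 points in either direction.

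**The case against.** The best defence is that the day-10 sentence preserves data. Day 10 is the end of treatment and the time point of the primary outcome, so the sentence can be read as an instruction to obtain that evaluation despite withdrawal. Study drug is given only for 10 days, so most need for unblinding plausibly falls in the period the rule covers. What is planned after day 10 is secondary: Interventions names only angina and TCM score for follow-up, and places the ECG and laboratory tests at enrolment and end of treatment. All of this stands and limits the weight of the point. It does not remove the conflict with the 8-week plan, the lack of an instruction after day 10, or the interaction with the FAS.

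A reader might go further in four ways that the documents do not support:

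- *That the outcome of the emergency is lost.* The CRF must hold its cause, time, handling and result, and the patient remains in the safety set.
- *That data are closed at day 10 and never recorded afterwards.* The text says neither. This is an inference from withdrawal; what can be said is that no later collection is provided for.
- *That the rule removes the most serious cases.* It covers only emergencies that lead to unblinding. Withdrawal criteria separately removes other patients with serious deterioration or serious adverse events.
- *That 85% of the information is lost.* The ratio 56/66 = 85% counts calendar days, most of which carry no scheduled measurement beyond the patient diary.

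The condensed article may leave detail to a full protocol, but here it states a rule, and that rule conflicts with other sections of the same article.

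**Conclusion.** The point holds in a limited form. The protocol withdraws every patient unblinded in an emergency and provides only for a day-10 record. This conflicts with the planned 8-week collection of angina frequency and TCM score, and the rule cannot be applied to an emergency after day 10. The missing later course is related to outcome. For a patient whose dosing ends before day 10, the FAS definition extends the problem to the primary analysis.

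The number affected is probably small, but this is an assumption because no rate is given. The effect on power is negligible under any plausible loss. The shift of about 2 points in the illustration rests on assumed counts and on the extreme assumption that all dropped patients are failures. The weakness is selective missing data; it is not fatal to the trial and is cheap to correct.

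**What to change.** Reconcile Emergency unblinding, Interventions, The average frequency of angina pectoris, and Data management and statistical analysis, stating that:

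- unblinding alone does not end data collection;
- the patient is followed to week 8 for angina, TCM score and adverse events, whenever the emergency occurs, unless consent is withdrawn;
- the patient is analysed in the randomised arm and is included in the FAS regardless of the number of days dosed;
- data collected after unblinding are flagged, and a sensitivity analysis is run without them.

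The FAS change is essential, because without it the new rule does not reach the primary analysis. Withdrawal criteria should be checked for consistency, since a patient with an emergency may also meet one of those criteria. Nothing is proposed on whether study drug continues.

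The cost is a few sentences in the protocol, a few extra follow-up contacts, and some data that may no longer be blinded.
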